### Data management and analysis

Data from all study sites are pseudo anonymized and combined in an online data platform (handled by INCLIVA). Erasmus University Medical Center is responsible for analysis and reporting. As the project will collect health-related data, special attention is attributed to the role of each partner in terms of controllers and processors, and to the organizational and technical measures to be put in place to ensure General Data Protection Regulation (GDPR) compliance. In addition, the risks associated to data processing will be defined in the Data Protection Impact Assessment (art. 35 GDPR) to be evaluated together with the Controllers’ Data Protection Officers. The data management plan includes procedures for ensuring a high-quality data standard, according to the FAIR principles: Findability, Accessibility, Interoperability, and Reusability [41]. All data are handled confidentially and scientific data are stored anonymously.

Descriptive statistics are used to describe participant characteristics in each study site and in the total study population, and to describe implementation outcomes in the study sites. Differences between T0, T1, T2 and T3 measurements are evaluated using multilevel linear regression analyses for continuous outcome variables and multilevel logistic regression analyses for dichotomous outcome variables. Interaction tests are performed for age, gender, living situation and education level to evaluate effects in subgroups. Statistical analyses are repeated for each study site separately. We consider a *P*-value of 0.05 or lower to be statistically significant. Analyses are performed according to the ‘intention to treat’ principle. An additional per protocol analyses is performed to evaluate the impact of the dose of the intervention received on outcomes.

A preliminary cost-effectiveness analysis is performed with the baseline measurement as control condition from a healthcare perspective. The healthcare costs per individual participant are calculated by multiplying resource use (e.g., doctor appointments, hospital admissions) with corresponding unit prices if available. Utility values are calculated using the EuroQol 5-level EQ-5D (EQ-5D-5L) to estimate the quality-adjusted life years (QALYs) [27]. EQ-5D-5L has demonstrated good measurement properties such as ceiling effects, reliability, and sensitivity [42].

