### Study population and eligibility to participate in the study

All participants who provide informed consent are enrolled in the study. We aim to include 1750 participants in total. Each study site allocates at least 125 participants to the intervention condition and 125 participants to the control condition. Detailed numbers of participants per study site are presented in Table 1. Study sites might apply randomization at individual or cluster level to create intervention and control condition.

Study participants are included if they: (i) are aged ≥ 18 years old, (ii) are in a vulnerable situation (e.g. unemployed, low income, single parents, parents with dependent children, seniors (65 +) with dependency conditions, seniors (65 +) living alone, people with disabilities attended by social services, belonging to a minority, migrant situation), (iii) living in energy poverty conditions, and (vi) belonging to the recruitment sites identified by the local partners for the study. The research assistant recruits potential participants in collaboration with local agencies that work in the catchment area. Together they determine energy poverty conditions (criterion iii), based on their knowledge of and experience with the target population. The primary indicators suggested by EU Energy Poverty Observatory (EPOV) are used as guideline to assess the energy poverty status. EPOV established the following criteria:i.arrears on utility bills;ii.low absolute energy expenditure (below half of the national median (M/2));iii.high share of energy expenditure in income (double of the national median share of energy expenditure in income (2 M)) andiv.inability to keep home adequately warm [26].

Persons are not eligible to participate if they have previously been beneficiaries of a previous similar intervention, cannot adequately participate in the intervention actions proposed in the study site (e.g. intellectual disabilities, severe language limitations) or are illegally connected to the electricity grid.

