### Power consideration

WELLBASED counts with a total sample size of 1750 participants (*n* = 875 intervention group and *n* = 875 control group) distributed among the six study sites, with a minimum of 125 participants per arm per study site, as shown in Table 1. A 20% loss to follow-up (e.g. due to mortality, rehousing or impossibility to participate, as reflected in for this type of long-term studies) is expected [40]. This means the sample consists of *n* = 700 in the intervention group and *n* = 700 in the control group (total *n* = 1400) at 18-month follow-up. Equal standard deviations in the intervention and the control group are assumed, with alpha of 0.05 and power of 0.80. Thus, given six study sites with each an intervention group and control group, applying a correction factor to account for the clustered design, assuming an average cluster size of 117 citizens (1400/12) and an intra-class correlation coefficient of 0.02. For this expected overall sample size and assumptions, with regards to the continuous outcome measures (in particular, HRQoL) a difference of 0.28 standard deviation (SD) between the intervention and the control group can be detected at follow-up. This means that both at the European level, and in addition in each study site separately, small differences regarding the outcomes in the intervention group compared to the control group can be shown.

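### Site-level tests at 0.05 are planned for every site, although by the plan's own cluster definition a site has one cluster per arm; where that layout holds, the P-value cannot separate the programme from the group

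*Protocol article*

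**What the plan says.** Three parts of the protocol article bear on this.

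- **Power consideration.** The clusters are the arms within sites: "given six study sites with each an intervention group and control group, applying a correction factor to account for the clustered design", and "assuming an average cluster size of 117 citizens (1400/12) and an intra-class correlation coefficient of 0.02". The section ends by claiming that small differences can be shown at European level and also in each site on its own.
- **Data management and analysis.** The models are multilevel linear or logistic regressions whose levels are not named. The site-level repeat and the threshold then stand side by side: "Statistical analyses are repeated for each study site separately. We consider a *P*-value of 0.05 or lower to be statistically significant". Nothing exempts or qualifies the site-level tests.
- **Study population and eligibility to participate in the study.** "Study sites might apply randomization at individual or cluster level to create intervention and control condition". Randomisation is therefore optional and its unit is open. The Study design section speaks of catchment areas of an intervention or control site, which suggests area-based arms at some sites at least.

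**The concern.** By using 12 site-by-arm clusters with a positive ICC, the plan assumes that two groups can differ for reasons unrelated to the programme. Across six sites there is replication of such groups. Inside one site, under that definition, there is one group per arm. The group effect and the arm effect are then the same contrast, and zero degrees of freedom remain for the between-group variance. Calling the model multilevel does not supply them. The test measures the difference only against variation between persons, so it asks whether these two groups have equal means. The hypothesis in the article is about the programme.

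A city could therefore report that the programme works, or harms, because its two groups differed anyway. The article intends its results for local authorities and policy-makers, who are likely to look first at their own site. A larger site sample does not help: with one group per arm, more persons per group raise the false-positive rate.

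**Working it through.** **Inputs from the article:** 700 per arm at 18 months, mean cluster size 117, ICC 0.02, alpha 0.05, power 0.80, 20% loss, and the Table 1 sizes per arm (177, 156, 125, 146, 125, 146). Two-sided testing is assumed, since sidedness is not stated.

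**1. The plan's own figure.** Design effect DE = 1 + (117 − 1) × 0.02 = 3.32. Detectable difference = 2.80 × √(2 × 3.32 / 700) = 0.273 SD, against the stated 0.28. Without clustering it would be 2.80 × √(2 / 700) = 0.150 SD. The stated figure therefore does rest on the 12 site-by-arm clusters.

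**2. One group per arm, full ICC between the arms, cross-sectional test.** The true variance of the arm difference is DE times what the person-level test assumes, so the null rejection rate is approximately 2 × [1 − Φ(1.96 / √DE)]. At m = 117 this is 2 × [1 − Φ(1.96 / 1.822)] = 0.282. A simulation of a t-test that ignores the group effect gave 0.285.

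By site, after 20% loss:

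| Enrolled per arm | Completers per arm | DE | Rejection rate |
|---|---|---|---|
| 125 (two sites) | 100 | 2.98 | 0.256 |
| 146 (two sites) | 116.8 | 3.32 | 0.282 |
| 156 | 124.8 | 3.48 | 0.293 |
| 177 | 141.6 | 3.81 | 0.315 |

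The mean over the six rows of Table 1 is 0.281.

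**3. Only part of the ICC arm-specific (assumed shares, m = 117).** A component shared by both arms of a site cancels within the site. Half (0.01): DE 2.16, rate 0.182. A quarter (0.005): DE 1.58, rate 0.119.

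**4. Several clusters per arm, not modelled (m = 117/k).** k = 2: 0.181. k = 3: 0.140. k = 5: 0.103.

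**5. Change from baseline (assumed autocorrelations, m = 117).** With cluster autocorrelation c and person autocorrelation p, the ICC of the change is 0.02(1 − c) / [0.02(1 − c) + 0.98(1 − p)]. This goes into the same DE and rate formulas.

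| c | p = 0.5 | p = 0.7 |
|---|---|---|
| 0.5 | 0.282 | 0.372 |
| 0.8 | 0.159 | 0.220 |
| 0.9 | 0.106 | 0.142 |
| 0.95 | 0.078 | 0.097 |
| 1.0 | 0.050 | 0.050 |

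Taking change removes person-level variance as well as group variance, so the rate can go up as well as down.

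**6. Individual randomisation with no group-level component.** DE = 1 and the rate is 0.05.

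**7. The single-site power claim.** The 0.28 SD is the pooled figure. With no clustering at all, one site can detect 2.80 × √(2 / 141.6) = 0.33 SD to 2.80 × √(2 / 100) = 0.40 SD.

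**The case against.** The strongest case against is that one cluster per arm comes from a planning design effect and not from a stated allocation. Sites may randomise individuals, and Table 1 names several areas at some sites: three districts in Valencia, two in Heerlen, five neighbourhoods in Edirne. The article does not say how the ICC splits between a component shared by both arms and an arm-specific one. The main outcome is change in quality of life, so stable group differences cancel. The Limitations section says confounders will be measured and concedes that confounding may remain. The model levels may be set out in an analysis plan that is not shown.

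Much of this stands, and it limits the size. A reader might infer that every site's test has a 28% error rate, or compound the site rates into a chance that at least one of six sites is falsely significant. The documents support neither reading, because nowhere do they say that all six sites have one group per arm.

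The core remains. The article itself fixes the rule, repeating the analyses by site at 0.05, and applies it to all sites whatever their allocation. Naming the model levels cannot create replication where each arm is a single group. Adjusting for measured confounders may reduce the group component but does not guarantee 5%. Several clusters per arm help only if they are modelled.

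**Conclusion.** The concern holds conditionally. At any site that does not randomise individuals, or several clusters per arm with cluster in the model, the planned site-level test confounds the programme with the group and has no valid estimate of between-group variance. Under the plan's own cluster definition, with the full ICC of 0.02 acting between the two arms, a cross-sectional test has a false-positive rate of about 28% (26% to 32% by site) against a nominal 5%.

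That figure is one scenario. Under the assumed alternatives above, the rate is lower if the ICC is partly shared between arms. For change from baseline it runs from about 8% to 37% over cluster autocorrelation 0.95 to 0.5 and person autocorrelation 0.5 to 0.7. It returns to 5% under individual randomisation with no group component. Which scenario applies at which site cannot be told from the article, and that is why an unqualified test at all six is a poor rule.

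**What to change.** Reconcile the sections on study population, power and analysis:

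- **Allocation.** State for each site the unit of allocation, whether it is randomised, and the number of clusters per arm.
- **Analysis.** Limit the site-level test at 0.05 to sites that randomised individuals, or several clusters per arm with cluster in the model. At other sites, report the baseline-adjusted site-specific difference with its interval as descriptive, without a significance claim. State there that the interval does not cover between-group differences unrelated to the programme.
- **Power.** Remove or qualify the claim that small differences can be shown within single sites.

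Do not present a site-by-arm term in the pooled model as a cure, since it keeps the same confounding. Widening intervals by the site-by-arm variance is no cure either: that variance mixes group noise with real differences in effect, because the programme is adapted to each site.

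The cost is wording only, with no new data. The downside is that some sites can no longer report a significant local result.

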**Methods:**

A controlled trial is performed. A total of 875 participants are recruited (125–177 per study site) to receive the WELLBASED intervention programme for 12 months (intervention condition) and 875 participants act as controls (control condition). Data will be collected with a baseline measurement at inclusion (T0), and follow-up measurements after 6 months (T1), 12 months (T2), and 18 months (T3). In both study arms, effects of the WELLBASED intervention programme are measured: health-related quality of life (HR-QoL), mental health, frailty in older adults, self-perceived health, chronic conditions, and care utilization. At the same time points, household expenditure on energy and energy consumption are obtained. In the intervention arm, health-monitoring data (i.e. peak flow, oxygen saturation, blood pressure, and heart rate) are obtained monthly and sleep quality with a three-month interval. Household data with regard to temperature, humidity and air quality are collected near real-time by home sensors. Qualitative interviews are conducted in each study site to evaluate the impacts of the WELLBASED intervention programme and to help explain findings.

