### Objectives

The aim of this study is to evaluate the WELLBASED intervention programme, using a controlled trial design. The short, and mid-term effects of the programme on energy poverty and health and wellbeing indicators are evaluated in comparison to a control condition (i.e. no specific programme to address energy poverty is applied). Cost-effectiveness of the intervention programme is assessed. Furthermore, differential impact of the intervention programme with regard to gender and social determinants is explored. Additionally, interviews and focus groups are implemented in each study site to evaluate the impact of the intervention programme and to help explain outcomes. To this end, the controlled trial design is combined with a qualitative approach that offers explanations of the impact and implementation of the WELLBASED intervention programme.

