### Study design

A controlled trial is performed with an intervention condition and a control condition (i.e. no specific programme to address energy poverty is applied) in six study sites in Europe. Measures are taken at baseline (T0), at 6 months (T1), at 12 months (T2) and 18 months after baseline (follow-up; T3) in both research groups. In addition, in the intervention condition additional frequent monitoring of health and housing conditions takes place. Moreover, qualitative interviews with a subsample of participants undergoing the intervention condition take place near the beginning of the intervention (3–6 months) and after termination of the intervention (15–18 months).

The WELLBASED intervention programme targets adults ≥ 18y in vulnerable situations, living in energy poverty conditions that belong to one of the study sites. An overview of study sites and the target population is presented in Table 1. Local organisations (e.g. the social services department or an non-governmental organisation (NGO) that supports vulnerable groups) or the local research team, depending on study site, select eligible individuals. Recruitment of study participants and baseline data collection is scheduled to commence in autumn 2022. Potential participants in the catchment area of an intervention or control site receive information about the study and an invitation to provide informed consent to join the study by the study site team. Generally, in each selected household, the person who is considered responsible for the accommodation or best placed to provide the information is invited to join the study and to complete questionnaires. This participant is also invited to participate in health data collection and, when applicable, to join qualitative interviews at a later stage. In some cases more than one person per household may be invited to join the study. Participants only join the study after they have provided informed consent. Study participants, intervention providers and research assistants are not blinded due to the nature of the intervention. The study is performed in accordance with the capacity, organizational and contextual factors of each of the six participating cities, as described below.

**Table 1 Tab1:** Study site characteristics

STUDY SITE	RECRUITMENT OF PARTICIPANTS	
	**TARGET GROUP**	**NUMBER OF PARTICIPANTS**

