#### Data collection in both study arms

Individual level data on health, wellbeing and energy-poverty indicators in both research groups are collected through questionnaires completed by the participating adults (self-report). The questionnaires can be completed on paper or digitally through a secured mobile or web-based application. Instruments for which no validated translations are available will be translated (forward and backward translations). Before the start of the study, the questionnaire is pilot-tested to ensure its user-friendliness in terms of appropriateness, comprehensibility and length.

Instruments and variables collected in both study arms are presented in Table 2.

**Table 2 Tab2:** Instruments and variables collected in both study arms

Variable	Instrument/indicator	Data source	Timeline
**Sociodemographic details: age, sex, gender, occupation, etc**	Ad-hoc questionnaire	Online/offline self-reported questionnaire	Baseline

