**ENERGY EFFICIENCY EVALUATION**			
**Energy consumption**	On grid (e.g. electricity, gas, heat) and off-grid (e.g. bottled gas, coal) energy consumption	Online/offline self-reported questionnaire, if possible, smart meters or energy provider	Baseline, 6, 12 and 18 months
**Household income spent on different sources of energy**	% of income/Euros	Online/offline self-reported questionnaire and, if possible, energy provider	

The main outcome is the change in health-related quality of life (HrQoL). This is measured by the EuroQol 5-level EQ-5D (EQ-5D-5L) instrument [27]. Secondary outcome measures include satisfaction with life, mental health, outcomes related to lifestyle behaviour, comorbidities, loneliness, subjective comfort in households, control over life, and social support. Frailty is assessed in older adults. Energy-related outcome measures are energy poverty indicators as defined by EPOV [26], attitudes towards adoption of energy efficiency measures, and coping behaviours.

Additional data on health care use are collected through electronic health records (when possible) for both intervention and control condition. This entails visits to the emergency ward and relevant care use outcomes. If data is not available through the electronic health records this information is obtained in the self-reported questionnaire.

Household spending on energy and energy consumption is obtained for participants in the intervention and control condition via the self-reported questionnaire. Depending on the study site additional data may be collected via smart energy meters or via energy providers.

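### The cost-effectiveness analysis takes baseline as its comparator although the trial has a concurrent control arm with the same utility and care-use data, so changes common to both arms count as programme effect

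*Protocol article*

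**What the plan says.** The Objectives section evaluates programme effects against a "control condition (i.e. no specific programme to address energy poverty is applied"), and then adds the economic aim without qualification: "Cost-effectiveness of the intervention programme is assessed". The abstract gives the size of the comparison arm: "875 participants act as controls (control condition").

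The economic comparison itself appears only under Data management and analysis: "A preliminary cost-effectiveness analysis is performed with the baseline measurement as control condition from a healthcare perspective". The same paragraph derives QALYs from the EQ-5D-5L and builds costs from resource use multiplied by unit prices.

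The data are gathered alike in the two arms. Study design schedules measurements at baseline, 6, 12 and "18 months after baseline (follow-up; T3) in both research groups". Data collection in both study arms says: "Instruments and variables collected in both study arms are presented in Table 2". That table lists the EQ-5D-5L and the health care use measures. The text below the table adds: "Additional data on health care use are collected through electronic health records (when possible) for both intervention and control condition".

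**The concern.** The economic analysis uses a different meaning of control from the rest of the trial. The effect analyses set the intervention arm against people followed over the same period. The economic analysis sets follow-up against the starting point, and the article gives no reason for the difference.

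A before-after contrast cannot separate the programme from anything else that moves over 18 months. Three mechanisms deserve mention, in order of weight:

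- **Time trend.** The Background section itself names rising energy prices as a driver of energy poverty. Prices and energy policy can move health and care use in both arms during follow-up.
- **Season.** The Study design section says: "Recruitment of study participants and baseline data collection is scheduled to commence in autumn 2022". For those recruited then, the 6- and 18-month visits fall about half a year out of phase with baseline.
- **Regression to the mean.** This is possible but indirect. Some entry indicators, such as utility arrears or a cold home, describe a current adverse state that may ease by itself.

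Cost-effectiveness is a stated objective, and the results are meant for policy-makers and local authorities. A cost per QALY on this basis could disagree with the trial's own controlled estimate on the same instrument, the EQ-5D-5L, which is also the main outcome.

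**Working it through.** The plan gives no economic figure, so there is none to reproduce. The check is whether a change shared by both arms drops out of the comparison.

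**Inputs from the article.** Visits at t = 0, 0.5, 1.0 and 1.5 years in both arms; utilities from the EQ-5D-5L.

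**Assumed input.** A mean utility change c common to both arms and unrelated to the programme. The article gives no value. I use c = ±0.02, with ±0.05 as a wider case.

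**Formula.** By the trapezoidal rule with half-year steps, QALYs gained relative to a flat baseline are 0.5 × [(u0+u1)/2 + (u1+u2)/2 + (u2+u3)/2], where u is the departure from baseline utility at each visit.

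**Shared change under a baseline comparator, over 18 months:**

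- Linear drift reaching c at T3, u = (0, c/3, 2c/3, c): 0.5 × (c/6 + c/2 + 5c/6) = 0.75c. This is ±0.015 for c = ±0.02, and ±0.0375 for c = ±0.05.
- Step from T1 onward, u = (0, c, c, c): 0.5 × (c/2 + c + c) = 1.25c. This is ±0.025, and ±0.0625.
- Seasonal offset at T1 and T3 only, u = (0, c, 0, c): 0.5 × (c/2 + c/2 + c/2) = 0.75c. This is ±0.015, and ±0.0375.

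**Shared change under the concurrent comparator.** Both arms carry the same term, so the difference is 0 in all three cases.

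**What this could do to a cost per QALY.** Assume a true incremental gain of 0.02 QALY and an incremental cost of 500 currency units; neither figure is in the article.

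- Concurrent comparator: 500 / 0.02 = 25,000.
- Baseline comparator, shared drift of +0.015 QALY: 500 / 0.035 ≈ 14,300.
- Baseline comparator, shared drift of −0.015 QALY: 500 / 0.005 = 100,000.

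A shared change in care use would enter the cost difference in the same way. These figures show the mechanism and the sensitivity; they do not predict the bias in this trial.

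**The case against.** **The analysis is called preliminary, and the main comparison is untouched.** Both are true, and they limit the weight of the point. But the Objectives section states the aim without that label, and the article describes no later, controlled economic analysis. A fuller economic plan may exist; that would not alter the comparator this text fixes.

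**The control arm may not be randomised.** Under Study population and eligibility, sites might randomise, individually or by cluster; the Limitations section concedes possible confounding; and controls may be given money or groceries. So a between-arm analysis brings in arm differences that a before-after analysis does not have. This stands, and it is why adjustment is needed. It does not favour baseline as comparator: the effect analyses rely on the same controls, and the concurrent arm still removes shared change. Waitlisted controls receive the programme only after data collection ends, so they remain valid comparators through T3.

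**Season is only part of the story.** This also stands. Baseline collection begins in autumn 2022, but the article does not say that all baselines fall then. The 12-month visit is roughly in phase with baseline, so only the 6- and 18-month values, and QALYs accumulated through them, are exposed.

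**Stronger readings that the article does not support.** A reader might infer a sizeable regression to the mean and express it as a share of the 0.28 SD in the power section. The article gives neither a baseline shortfall nor a test-retest correlation. Entry is not on EQ-5D-5L or care use, and many vulnerability criteria (disability, minority status, single parenthood) are lasting. The 0.28 SD is also a detectable between-arm difference, not a target of the economic analysis. A reader might likewise infer that control data are excluded from all economic work, but the text does not say so. That the comparison is with the intervention arm's own baseline is the natural reading, though not spelled out.

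**Conclusion.** The point holds as a conflict between the stated economic comparator and the trial's own control condition. Followed as written, the analysis attributes to the programme whatever changed in both arms, although the trial plans to collect what is needed to remove that change. The direction of the bias is unknown and its size cannot be derived from the article. The illustrative shift of ±0.015 to ±0.025 QALY over 18 months rests entirely on an assumed shared utility change of ±0.02.

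This should be fixed, but it does not threaten the trial's main result: it concerns one further objective, carries a preliminary label, and leaves the controlled analysis of health-related quality of life intact. Nor would the change remove all bias. It removes change common to both arms and leaves residual confounding where sites do not randomise.

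**What to change.** In Data management and analysis, replace the baseline comparator with the concurrent control arm. Suggested wording: *The cost-effectiveness analysis compares the intervention arm with the concurrent control arm, from the perspective of the healthcare system. Incremental costs and incremental QALYs are estimated between arms, adjusted for baseline utility, baseline costs, study site and the measured confounders. A before-after comparison is reported only as a descriptive supplement.*

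If the before-after analysis is kept as an early look for practical reasons, the text should say so, and should state that the cost-effectiveness objective is answered by the between-arm analysis.

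The cost is a change of wording and slightly more analysis work. No new data are needed, because both arms already supply utilities and care use at all four time points. The remaining weakness is residual confounding at sites that do not randomise, which the effect analyses already share.
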